#### Exclusion criteria

Exclusion criteria are as follows: (1) patients with RD with other types of holes except MH, choroidal detachment, obvious proliferative vitreoretinopathy, intraocular haemorrhage, severe cataract, glaucoma, retinal vascular inflammation or obstruction, macular degeneration, macular neovascularisation, macular haemorrhage, pathological myopia and macular atrophy; (2) patients with previous history of intraocular surgery (including PPV and intravitreal drug injection); (3) patients whose general condition cannot tolerate the operation; (4) patients who cannot cooperate with the examination and follow-up for <6 months; (5) patients unwilling to undergo concurrent vitrectomy and cataract surgery; (6) patients with concomitant diseases or conditions of the target eye or whole body (including malignant hypertension; AIDS; malignant tumour; serious mental, cardiovascular, neurological, respiratory, digestive or other systemic disease; long-term use of hormones; and immunodeficiency after heart stenting or organ transplantation); (7) patients with diabetes with poor blood glucose control; (8) patients with poor communication skills and compliance; (9) patients without the ability to follow the postoperative position; and (10) participation in other trials.

#### Withdrawal criteria

Withdrawal criteria are as follows: (1) loss to follow-up; (2) withdrawal of informed consent; (3) participation in other clinical studies during the study; (4) emergence of other eye diseases during the study; (5) need of other eye treatments during the study; (6) decision by researchers to withdraw participant due to safety concerns; and (7) decision by researchers to withdraw patient due to unsuitability of treatment methods (including remedial treatment) for patient.

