### Postoperative management

All patients will be administered with anti-inflammatory and anti-infective treatment after operation. During hospitalisation, IOP will be monitored two to three times daily. If IOP increases, it will be reduced. In case it is not controlled, mannitol will be administered intravenously to control IOP. If necessary, anterior chamber puncture, aspiration and drainage or glaucoma surgery will be performed.

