### Safety and combined operation-related adverse events

Possible phacoemulsification and intraocular lens implantation combined with vitrectomy complications include intraocular haemorrhage, suprachoroidal haemorrhage, endophthalmitis, uveitis, intraocular lens dislocation and corneal endothelial decompensation. Lens capsule flap transplantation may increase the risk of rejection, although the capsule flap will be immersed in sterile distilled water for 30 min. However, to date, no adverse reactions caused by lens capsule flap transplantation for the treatment of MH have been reported. During the trial, we will record and analyse any surgery-related adverse events (including the type and number) in each group and possible causes. Patients will receive appropriate intervention for any adverse events that occur during the treatment and follow-up phases. Severe adverse events will be reported immediately to the primary investigator, and affected participants will be withdrawn from the study.

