### Sample size

Although no RCT of lens capsule flap transplantation in the treatment of HMMHRD has been reported, according to the existing published papers^23 29^ related to this study, the type I closure rate in the experimental group was expected to be 96.0%, whereas the rate in the control group was should be 65.0%. An a priori power analysis conducted using a two-tailed test (power=0.8) at the 5% significance level indicated that 21 participants are required in each group. Considering the attrition rate of 20%, the sample size in each group was determined as 27. With the 1:1 allocation, 54 participants will be recruited.

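### The withdrawal rules can remove some surgical failures from the month-6 comparison and end safety follow-up after a severe adverse event

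*Protocol article*

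**What the plan says.** Under Withdrawal criteria, the protocol article lists seven grounds. Loss to follow-up and withdrawn consent stand beside new eye disease (criterion 4), "5) need of other eye treatments during the study; (6) decision by researchers to withdraw participant due to safety concerns", and "decision by researchers to withdraw patient due to unsuitability of treatment methods (including remedial treatment) for patient". Table 1 applies the withdrawal criteria at every visit from the day before surgery to month 6.

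Under Safety and combined operation-related adverse events: "Severe adverse events will be reported immediately to the primary investigator, and affected participants will be withdrawn from the study". The same section says that "Patients will receive appropriate intervention for any adverse events that occur during the treatment and follow-up phases" and that "we will record and analyse any surgery-related adverse events (including the type and number) in each group and possible causes".

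Postoperative management foresees further eye procedures for raised pressure: "If necessary, anterior chamber puncture, aspiration and drainage or glaucoma surgery will be performed".

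The primary outcome is type I closure at 6 months. Under Sample size: "Considering the attrition rate of 20%, the sample size in each group was determined as 27". No section says that withdrawn participants continue assessments, have a month-6 OCT, or count in any particular way.

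**The concern.** The study treatment is a single operation. Once it is done there is no continuing treatment to stop, so withdrawal here can only mean that observation stops. Several triggers can be consequences of how the operation went. A reopened hole or redetachment may need another procedure, a complication may be a new eye disease, and a severe adverse event may come from the surgery. Withdrawal on these grounds before month 6 is then linked to the outcome being measured.

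Two things are at stake. First, eyes that leave because they did badly raise the observed closure rate in their arm. Depending on how this falls between the arms, it can shrink a real difference or produce a false one. Second, the stated objective includes safety, yet follow-up ends for the participants whose later course matters most for it.

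This is a rule of conduct, not a gap left to an analysis plan. Such a plan can define analysis sets and imputation, but it cannot recover visits that were never made.

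**Working it through.** **Inputs from the protocol article.** Type I closure 96% v 65%, two-sided 5%, power 0.80, 21 per group, 20% attrition, 27 per group (Sample size); 1:1 allocation (Trial design); Fisher's exact test (Statistical analysis).

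**The plan's own figure.** For two proportions the arcsine formula gives 21.06 per group and the unpooled-variance formula 21.7. Both are close to the stated 21. For attrition, 21/0.8 = 26.25, rounded up to 27. The figure is reproduced and is not disputed here.

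**Expected failures.** Not type I at month 6: 27 × 0.04 = 1.08 experimental and 27 × 0.35 = 9.45 control. Together that is 10.53 of 54, or 19.5%, about as large as the whole 20% attrition allowance.

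**Assumption.** The documents do not say what share *f* of failures would be withdrawn, so a range is shown. With true rate *p*, the observed rate among eyes that remain is

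*p* / (*p* + (1 − *p*)(1 − *f*)).

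For example, at *f* = 0.5: 0.96/(0.96 + 0.04 × 0.5) = 0.980 and 0.65/(0.65 + 0.35 × 0.5) = 0.788.

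**Equal share withdrawn in both arms, true rates 96% v 65%** (27 randomised per arm, Fisher p < 0.05, 40,000 simulated trials):

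| Share withdrawn | Observed rates | Gap (points) | Power |
|---|---|---|---|
| 0% | 96.0% v 65.0% | 31.0 | 76.6% |
| 10% | 96.4% v 67.4% | 29.0 | 76.9% |
| 25% | 97.0% v 71.2% | 25.7 | 72.5% |
| 50% | 98.0% v 78.8% | 19.2 | 51.9% |
| 75% | 99.0% v 88.1% | 10.8 | 16.9% |

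**No true difference, 65% in both arms** (same simulation; last row 20,000 trials):

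| Withdrawn, experimental v control | False gap (points) | False-positive rate |
|---|---|---|
| 0% v 0% | 0 | 2.6% |
| 50% v 50% | 0 | 3.2% |
| 25% v 0% | 6.2 | 5.5% |
| 50% v 25% | 7.6 | 5.9% |
| 50% v 0% | 13.8 | 13.9% |
| 80% v 0% | 25.3 | 44.6% |

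**Would such losses stand out?** Half of all failures at 96% v 65% is 0.5 × (0.04 + 0.35)/2 = 9.75% of participants. The extreme last row is 0.8 × 0.35/2 = 14%. Both lie inside the planned 20%, so the attrition count alone would not reveal the problem.

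**The case against.** A reader might infer more than the documents support, in five ways.

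- *All surgical failures leave.* They do not. A persistent hole or type II closure is not itself a withdrawal criterion. Anatomical measurement has an unclosed category, and type II closure at 6 months is a secondary outcome. An eye without further treatment stays and counts as not type I.
- *The safety data are lost.* The triggering event is recorded and analysed by group. What is lost is follow-up after it.
- *The withdrawal rule flatly contradicts Postoperative management.* That depends on the word *other* in criterion 5. It could mean treatment outside the protocol's own management. Two texts favour this narrower reading: all adverse events are to be treated but only severe ones lead to withdrawal, and criterion 7 seems to assume that some remedial treatment happens within the study. The wording is ambiguous and needs reconciling, but it is not a proven contradiction.
- *The sample size treats these losses as ignorable.* Sample size gives only a rate. It does not say what attrition comprises or how withdrawn participants are analysed.
- *The unblinded surgeon decides who is withdrawn.* The criteria say researchers, and all researchers except the surgeon are blinded. Nothing assigns the decision to the surgeon, and nothing excludes it.

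Two further objections carry weight. No text supports any particular share of failures withdrawn; at 10% equal withdrawal, power is essentially unchanged. And OCT is scheduled at every postoperative visit, so an analysis plan could count an eye known to have failed before withdrawal as a failure. That helps for retreated eyes. It does not help for an eye withdrawn early for a severe event or a new disease, whose month-6 state stays unknown, and it does not restore later safety visits.

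**Conclusion.** The concern holds in a limited form. Criteria 4 to 7 and the severe-adverse-event rule end study participation on grounds that can follow from surgical failure, and nothing in the article keeps these participants in follow-up to month 6. Some failures (those retreated, withdrawn by decision, or with a severe event) can therefore leave the primary comparison, and safety follow-up stops after the triggering event.

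The size rests on the assumed share withdrawn and on the plan's own closure rates. Equal withdrawal of up to half the failures costs between almost nothing and about 25 percentage points of power. It works against the experimental operation and does not inflate the false-positive rate above 5%. Inflation needs unequal withdrawal: modest in the 25% v 0% and 50% v 25% cases, 14% at 50% v 0%, and 45% only in the extreme 80% v 0% case. The direction of bias is not fixed. Enlarging the groups from 21 to 27 replaces numbers but does not correct bias.

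It should be settled before enrolment, because visits not made cannot be restored afterwards.

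**What to change.** Amend Withdrawal criteria and the safety section as follows.

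1. Only withdrawn consent or loss of contact ends follow-up. All other randomised participants, including those meeting criteria 3 to 7 or with a severe adverse event, stay in the scheduled visits, including the month-6 OCT and adverse-event recording.
2. Analyse all randomised participants as allocated.
3. State in advance how an eye retreated before month 6, and an eye without a month-6 OCT, counts. One option is to count it as not type I closure, with a sensitivity analysis for the missing ones. If an analysis plan already fixes items 2 and 3, a cross-reference is enough.
4. Reconcile criterion 5 with the eye procedures in Postoperative management and with the treatment of adverse events, so that it is clear which treatments the word *other* covers. The care given does not change.

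The cost is a short amendment, a few visits that are already in the schedule for participants who would otherwise be dropped, and possibly slightly lower reported closure rates. Trial status describes the study as still preparatory, so this can be done before the first participant is enrolled.

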### Randomisation and blinding

The stratified randomisation method will be adopted in allocating participants to the two groups in a 1:1 ratio using the central random system. The stratification factors are as follows: (1) MH size >400 µm and (2) MH size ≤400 µm. Except the surgeon, all researchers, including the outcome assessors, statisticians and data analysts, will be blinded to group assignment, but providers of the intervention/control will be informed by necessity. Vitrectomy combined with lens capsule flap transplantation or ILM tamponade will be performed by one experienced surgeon. Before the trial, researchers will be fully trained in the randomisation procedure and made aware of their individual responsibilities. The successful implementation and maintenance of the randomisation and blinding method will be validated.

### Interventions

All participants who meet the inclusion criteria of this study and do not meet any of the exclusion criteria can be included in this study. Before the surgery, the patients should receive complete preoperative ophthalmic examination, including best corrected visual acuity (BCVA), slit lamp inspection, axial length, presence of staphyloma, myopia dioptres, intraocular pressure (IOP), ocular B-ultrasound, OCT, multifocal electrophysiology (mfERG), MP-1 microperimeter, fluorescence fundus angiography and indocyanine green angiography. After passing the screening, the participants who provided written informed consent will be randomly assigned to two parallel trial groups in a 1:1 ratio according to the central randomisation system. The patients will undergo vitrectomy combined with lens capsule flap transplantation or ILM tamponade and regular postsurgery follow-up. Participants will be blinded to the specific surgical methods. The timeline of data collection is shown in table 1.

**Table 1 T1:** Outcome measurements and data collection at each follow-up timepoint

Phase		Screen	Preoperative examination	Postoperative follow-up					
Follow-up		1	2	3	4	5	6	7	14
Time points		Within 1 week before operation	One day before operation	1 day after operation	3 days after operation	7 days after operation	1 month after operation	3 months after operation	6 months after operation
Informed consent		●							
Inclusion and exclusion criteria		●							
Withdrawal criteria			●	●	●	●	●	●	●
Medical history collection		●							
Ophthalmic examination	BCVA	●	●	●	●	●	●	●	●
	Slit lamp inspection	●	●	●	●	●	●	●	●
	Axial length	●						●	●
	Presence of staphyloma	●						●	●
	Myopia dioptres	●						●	●
	IOP	●	●	●	●	●	●	●	●
	Ocular B-ultrasound	●	●	●	●	●	●	●	●
	OCT	●	●	●	●	●	●	●	●
	mfERG	●						●	●
	MP-1 microperimeter	●						●	●
	FFA and ICGA	●							●
Systemic	Vital signs	●	●	●	●	●	●	●	●
examination	Physical examination	●							●
Laboratory examination	routine blood test	●	●				●		●
	Blood biochemistry	●					●		●
	Coagulation function	●							●
	Urinalysis	●							●
	Immune and infection measurements	●				●	●		●
	ECG	●							●
	Chest CT	●							●
Adverse events recorded		●	●	●	●	●	●	●	●

BCVA, best corrected visual acuity; IOP, intraocular pressure; OCT, optical coherence tomography; mfERG, multifocal electrophysiology; FFA, fluorescence fundus angiography; ICGA, indocyanine green angiography.

### Experimental group

Patients will first undergo phacoemulsification and intraocular lens implantation. During this operation, the lens capsule flap will be obtained and placed in sterile distilled water for at least 30 min. Thereafter, the 23-gauge vitrectomy through the pars plana will be performed, and the ILM will be stained with brilliant blue. After brilliant blue staining, the ILM in the macular area will be completely removed with intraocular forceps. Then the small piece of lens capsule flap is moved into the vitreous cavity with microforceps trough the 23-gauge trocar. The trimming of lens capsule flap will be performed in the vitreous cavity, and the lens capsule flap can be directly placed above the MH surface. The capsular flap should be trimmed by vitrectomy cutter as round as possible, and its diameter is about twice that of the MH. Afterwards, the lens capsule flap will need to be inserted into the MH to complete gas–liquid exchange. In this process, the operator will ensure that the capsule flap is always right under the MH. Finally, silicone oil (Oxane 5700 Bausch & Lomb, Kingston-upon-Thames, UK) will be injected into the vitreous cavity.

### Control group

Patients will first undergo phacoemulsification and intraocular lens implantation. Thereafter, 23-gauge vitrectomy through the pars plana will be performed. After complete vitreous removal, ILM will be stained with brilliant blue. After brilliant blue staining, the ILM of the retina in the brilliant blue staining area will be directly clamped, and the ILM ring in the area will be removed about 1.5-disc diameters away from the MH. Care will be taken to prevent peeling off the ILM valve at the edge of the MH. Thereafter, the free ILM flap will be turned over and filled into the MH. During the operation, accurate filling of ILM into the MH will be confirmed severally. After complete gas–liquid exchange, silicone oil (Oxane 5700 Bausch & Lomb) will be injected into the vitreous cavity.

### Postoperative management

All patients will be administered with anti-inflammatory and anti-infective treatment after operation. During hospitalisation, IOP will be monitored two to three times daily. If IOP increases, it will be reduced. In case it is not controlled, mannitol will be administered intravenously to control IOP. If necessary, anterior chamber puncture, aspiration and drainage or glaucoma surgery will be performed.

### Outcome measurements

Follow-up will be conducted at 1, 3 and 7 days and 1, 3 and 6 months after surgery in both groups. Necessary examinations will be performed at each follow-up visit.

#### Anatomical measurement

OCT will be used to assess the retina and macula before and after surgery. According to the postoperative situation of retinal reattachment and MH closure, the surgical result will be classified as: (1) type I closure: the two ends of the MH are closely connected and close to the RPE layer without any obvious exposure of the RPE layer and subretinal fluid (SRF); (2) type II closure: the two ends of the MH are not connected, and the edge of the hole is closely attached to the RPE layer with a distance between the two ends. The exposed RPE layer can be observed without any obvious SRF; (3) unclosed: the two ends of the MH are not connected, and the edge of the hole is still raised and tilted away from the RPE layer. The SRF can be observed further.^27 28^

#### Functional measurement

Postoperative visual acuity, macular retinal function and macular retinal sensitivity are all important functional outcomes. (1) Central vision: BCVA; (2) macular retinal function: mfERG collects the retinal amplitude information caused by specific stimulation, forms a three-dimensional topographic map and collects P1 wave response density data for intuitive evaluation of macular retinal function; (3) macular retinal sensitivity: MP-1 microperimetry is used to examine the microvisual field of the macula.

### Primary outcome

The primary outcome is type I closure rate of MH 6 months after operation.

### Secondary outcomes

The following indicators will be used to comprehensively assess anatomical outcome: (1) type I closure rate of MH 3 months after operation; (2) type II closure rate of MH 6 months after operation; and (3) type II closure rate of MH 3 months after operation.

Functional outcomes will be assessed as follows: (1) changes in BCVA 3 and 6 months after operation compared with baseline; (2) changes in P1 wave response density in the macular region 3 and 6 months after operation compared with baseline; and (3) changes in macular retinal sensitivity 3 and 6 months after operation compared with baseline.

Furthermore, the number of adverse events and reactions, abnormality of ophthalmic examination, abnormal systemic symptoms and laboratory results will be recorded at each follow-up visit.

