**Trial registration number:**

ChiCTR2200057836.

Strengths and limitations of this studyThis is the first randomised controlled trial investigating the efficacy and safety of vitrectomy combined with lens capsule flap transplantation in the treatment of high myopia macular hole retinal detachment.In addition to anatomical measurement, functional measurements, including best-corrected visual acuity, macular retinal function and macular retinal sensitivity, are also used to evaluate the postoperative efficacy.Based on whether the macular hole reaches 400 µm, this trial will adopt the stratified randomisation method through the central random system.Strict quality control measures, including adequate concealment of randomised group allocations, will be implemented.Difference in preoperative lens opacity affecting the baseline visual acuity of the two groups and difficult evaluation of vitreoretinal surgery are the limitations of this trial.

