#### Inclusion criteria

The inclusion criteria are as follows: (1) patients ≥50 years old who were diagnosed as HMMHRD by indirect ophthalmoscopy, macular OCT, fundus photography and B-ultrasound examination; (2) equivalent spherical dioptre ≤–6.00 D or axis length ≥26 mm; (3) MH as main cause of RD; (4) turbid lens without obvious calcification in the lens capsule, requiring combination with cataract surgery; (5) the range of RD within the retinal vascular arch of the posterior pole; and (6) consent to undergo surgical treatment and regular follow-up and sign relevant informed consent.

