### Statistical analysis

SPSS (V.22.0; SPSS, Inc) and GraphPad Prism (V.8, GraphPad software Inc, San Diego, California, USA) will be used for data processing and analyses. Categorical variables will be expressed as numbers and frequencies, and between-group differences will be evaluated with Fisher’s exact test. Continuous variables will be expressed as the mean±SD. The Kolmogorov-Smirnov test will be used to determine whether continuous variables are normally distributed. The Student’s t-test will be used for normally distributed data, and the Wilcoxon signed-rank test will be used for non-normally distributed data. All statistical tests will be two-sided with p<0.05 considered statistically significant.

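### Functional outcomes are compared as unadjusted changes from baseline: valid under randomisation, but less precise than a baseline-adjusted analysis and more exposed to chance imbalance, above all for BCVA

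*Protocol article*

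**What the plan says.** **Outcomes.** Under Secondary outcomes, all three functional measures are changes from baseline: "1) changes in BCVA 3 and 6 months after operation compared with baseline", "changes in P1 wave response density in the macular region 3 and 6 months after operation compared with baseline" and "changes in macular retinal sensitivity 3 and 6 months after operation compared with baseline".

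**Analysis.** For continuous variables, Statistical analysis says that Student's "t-test will be used for normally distributed data, and the Wilcoxon signed-rank test will be used for non-normally distributed data". No covariate is named.

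**Baseline.** The strengths and limitations list gives as a limitation: "Difference in preoperative lens opacity affecting the baseline visual acuity of the two groups". The inclusion criteria require a "turbid lens without obvious calcification in the lens capsule, requiring combination with cataract surgery". The Experimental group section begins "Patients will first undergo phacoemulsification and intraocular lens implantation", and the Control group section begins with the same step.

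**Balance.** Under Randomisation and blinding, the only stratification factor is macular hole size (above 400 µm, or 400 µm and below). Neither baseline BCVA nor lens opacity is balanced by design.

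**The concern.** Every participant enters with an opaque lens and leaves surgery without it. Baseline BCVA therefore contains an opacity component that is absent at 3 and 6 months. A change score gives the baseline a weight of exactly one, so it carries all of that component into the comparison. This has two consequences.

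- **Precision.** A component present only at baseline weakens the correlation between baseline and follow-up. A low correlation is where a change score is least efficient.
- **Chance imbalance.** If one arm happens to have denser cataracts, its BCVA gain looks larger for reasons unrelated to the macular procedure.

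Better functional recovery is one of the two parts of the hypothesis in the Overview, and functional measurement is listed as a strength of the study. The article recognises the lens-opacity problem, but the analysis it states does nothing to reduce it.

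**Working it through.** **Inputs.** From Sample size: 21 per arm, 27 after allowing for 20% attrition (21/0.80 = 26.25, rounded up), 54 in total. As a check on the 21, the unpooled two-proportion formula for 96% v 65% gives (1.960+0.842)² × (0.96×0.04 + 0.65×0.35)/0.31² = 21.7, or 22, one more than stated. The article gives no figure for the functional outcomes: no SD, no correlation, no target difference. The within-arm correlation r between baseline and follow-up is therefore an assumption, shown over a range.

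**Step 1: precision with equal SDs.** In units of 2σ²/n, the variance of the between-arm difference is:

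- change score: 2(1−r)
- ANCOVA: 1−r² = (1−r)(1+r)
- ratio, change to ANCOVA: 2/(1+r)

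Estimating the slope inflates the ANCOVA variance by about 1+1/(N−4), which is 1.026 at N=42. The third column includes this. The last column is large-sample: for an effect that gives ANCOVA 80% power, the change-score test has power Φ(2.802×√((1+r)/2) − 1.960).

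| r | Excess variance of change score | Per arm needed to match ANCOVA with 21 | Power of change score when ANCOVA has 80% |
|---|---|---|---|
| 0.2 | +67% | 34.1 | 58% |
| 0.3 | +54% | 31.5 | 62% |
| 0.5 | +33% | 27.3 | 68% |
| 0.7 | +18% | 24.1 | 73% |
| 0.9 | +5% | 21.5 | 78% |

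**Step 2: opacity present at baseline only.** A simulation of 20,000 trials with 21 per arm and no treatment effect used a macular baseline and a follow-up value, each with SD 1 and correlated 0.7. Opacity noise was added to the baseline alone.

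| Opacity variance | Resulting r | SD of effect: change | ANCOVA | Follow-up value alone |
|---|---|---|---|---|
| 0 | 0.70 | 0.239 | 0.224 | 0.310 |
| 0.5 | 0.57 | 0.327 | 0.258 | 0.308 |
| 1.0 | 0.49 | 0.389 | 0.271 | 0.307 |

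The closed form agrees. At opacity variance 1.0 the change score has variance (1+2−1.4)×2/21 = 0.152, so SD 0.390. Once opacity variance reaches half the macular variance, subtracting the baseline is worse than ignoring it.

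**Step 3: bias.** Averaged over all simulated randomisations, every estimator was within 0.01 of zero.

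**Step 4: error given a chance imbalance.** The SD of the baseline difference between arms is √(2/n) baseline SDs: 0.309 at 21 per arm and 0.272 at 27. A difference beyond 0.3 SD in one direction or the other thus arises in about 33% and 27% of randomisations.

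- Baseline imbalance above 0.3 (in macular-baseline SDs): the change score was off on average by −0.14, −0.28 and −0.37 at opacity variance 0, 0.5 and 1.0. ANCOVA was off by less than 0.01.
- Imbalance above 0.2 in opacity itself: the change score was off by −0.33 and −0.39 at opacity variance 0.5 and 1.0. ANCOVA was off by −0.15 and −0.14. Adjustment thus removed 1−0.149/0.325 = 54% and 1−0.138/0.387 = 64% of the error.

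**The case against.** **The unadjusted comparison is valid.** This stands. A reader might infer from the limitation on lens opacity that the planned comparison is biased. Allocation is randomised 1:1, and Step 3 shows no bias on average. What differs is precision and the error in a trial that happens to be imbalanced.

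**A change endpoint is not a fault.** This stands too. ANCOVA on the change, with baseline as covariate, gives the same treatment effect as ANCOVA on the follow-up value. Secondary outcomes can stay as written; the remedy belongs in Statistical analysis.

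**The article concedes the problem for visual acuity only.** Correct. A reader might extend it to mfERG and microperimetry, but the document does not say that those baselines are distorted. For them the case rests on precision alone.

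**The eligibility criteria narrow the range of opacity.** Severe cataract is excluded, as is obvious capsular calcification. This limits the possible imbalance but does not remove it, and the article still lists the difference as a limitation.

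**The gain may be small.** At r=0.9 it is about 5%. A baseline-only opacity component pulls r down, so so high a value is less likely for BCVA, but the documents cannot settle it.

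**Covariates are often left to the analysis plan, and the tests are generic.** Statistical analysis does not tie the t-test to the functional outcomes by name, and an analysis plan that is not shown could add a covariate. But the article is not silent: it states a method for continuous variables, and that method is unadjusted.

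**Conclusion.** The point holds as one of efficiency and robustness in secondary outcomes. As stated, the analysis compares unadjusted changes from baseline. For BCVA that baseline carries, on the article's own account, a lens-opacity component that surgery removes in both arms. With equal SDs, the change-score variance exceeds that of ANCOVA by 67% at r=0.2, falling to 18% at 0.7 and 5% at 0.9. Where in that range the trial lies is unknown, because the article gives no correlation. Unequal SDs from opacity in the baseline would favour ANCOVA further, as Step 2 shows.

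It would be tempting to conclude that baseline adjustment solves the opacity problem. It does not. It deals with imbalance in measured baseline BCVA but, in the cases simulated, removed only about half to two thirds of the error from an imbalance in opacity itself. Table 1 lists slit-lamp inspection but no lens-opacity grade, so direct adjustment for opacity cannot be assumed to be available.

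The change is worth making because it costs little. It does not touch the validity of the trial, its primary outcome or its sample size.

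**What to change.** In Statistical analysis, add that BCVA, P1 wave response density and macular retinal sensitivity at 3 and 6 months will be compared between groups by ANCOVA. The covariates are the corresponding baseline value and the macular-hole-size stratum. Report the adjusted mean difference with its 95% CI. The dependent variable may be the post-operative value or the change from baseline, since the treatment effect is the same. BCVA is measured at two pre-operative visits in table 1, so name the one that serves as baseline.

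Keep the limitation on lens opacity in the report, because adjustment removes only part of that error.

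The cost is wording and about two degrees of freedom. Baseline values of all three measures are already collected under table 1, the stratum is known from randomisation, and SPSS fits the model. The primary analysis by Fisher's exact test and N=54 stay as they are.
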